### Surgery records and pathology assessment

The surgical specimens are preserved and processed according to the operation guidelines for pathological evaluation, and the pathological efficacy is assessed according to the TRG scoring criteria; the degree of radical cure and ypN staging are assessed according to the AJCC Version 8; at least the following information needed to be recorded:

- Length of operation
- Surgical method
- Tumor size
- Tumor site and the distance from the lower edge to the anus
- Number of lymph nodes detected
- Number of lymph node metastases
- Degree of eradication (RX/R0/R1/R2)
- Histological Type
- Microsatellite status (MSS/MSI-L/MSI-H)
- YpTMN staging (AJCC Version 8)
- Residual percentage of viable tumor cells in primary tumor (%)
- Pathologic response grading (TRG Criteria)
- Length of procedure is recorded
- Discharge time after surgery is recorded

## Follow-up Period

Following the end of treatment visit, the follow-up period is entered, which includes safety follow-up, tumor progression/recurrence, and survival follow-up.

Concomitant medications and concomitant therapies used for new or unresolved AEs related to trial treatment should be recorded after the end of treatment, up to 30 days after the last dose.

Adverse events should also be recorded until 30 days after the last dose after the end of treatment and followed up until resolution or stabilization of the adverse event.

Safety follow-up:

At 30 days (± 7 days) after the last dose of study drug, whether or not the subject starts a new anticancer therapy, the subject is required to return to the study site for safety follow-up or by telephone.

Follow-up of time to progression/relapse:

For subjects who do not have radiographic progression or recurrence at the end of treatment, radiographic assessments are performed at least every 3 months in Year 1 and at least every 6 months starting at Year 2 until radiographic progression or recurrence, receipt of other antineoplastic therapy, withdrawal of consent, loss to follow-up, or death.

Survival follow-up:

After the end of treatment, subjects will be followed for survival every 6 months until death, loss to follow-up, or the end of the study, whichever occurs first.

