## Secondary Endpoints

- Sphincter preserving rate：proportion of patients with preserved anal sphincter

Time Frame: instantly after surgery;

- Immune-related adverse event rate: adverse event rate that is deemed to be associated with PD-1 inhibition

Time Frame: from commencing of PD-1 inhibition to the 30th day after surgery;

- Treatment-related adverse event rate: adverse event rate that is deemed to be associated with all treatments

Time Frame: from commencing of treatment to the 30th day after surgery;

- Incidence rate of surgical complications: incidence rate of surgical complications within 30 days after surgery

Time Frame: within 30 days after surgery;

Exploratory Endpoints

- Longitudinal single-cell RNA-seq (scRNA-seq) and single-cell TCR-seq (scTCR-seq) of tumor tissue and matched peripheral blood to identify immune programs of response vs resistance

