# Study medication

## Overview of investigational product

In the study, study drugs are defined as Sintilimab.

|  | Sintilimab |
| --- | --- |
| Manufacturer | Innovent, China |
| Dose Form | Injection fluid |
| Strength | 100 mg |
| Route of Administration | Intravenous |

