**The specific dose and mode of administration are as follows:**

Sintilimab: 200 mg, every 3 weeks, with 21 days as a cycle. This product is for intravenous injection only. Intravenous infusion over 30 minutes. The infusion tube used in the infusion must be equipped with a sterile, pyrogen-free, low-protein-binding infusion tube filter (pore size 0.2-1.2 μm). This product should not be administered by intravenous bolus or single rapid intravenous injection. This product can be directly infused with 10mg/ml solution, or diluted with sodium chloride solution for injection (9mg/ml, 0.9%) or glucose solution for injection (50mg/ml, 5%), the concentration can be as low as 1mg/ml.

The study drug is administered until the protocol-specified treatment termination criteria occur.

Imaging assessment is performed for the subjects within 1 weeks of the last dose of Sintilimab therapy; surgery is performed for operable subjects 2 weeks after the last dose.

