### Reporting system of serious adverse events

It starts from signing of the informed consent until 30 days (inclusive) after the last dose of study drug. During the trial, in case of any serious adverse event, no matter initial report or follow-up report, the investigator should immediately report it to the relevant unit according to the regulatory requirements within 24 hours after being informed of the SAE.

For serious adverse events, the symptoms, severity, correlation with the investigational drug, time-of-onset, handled time, action taken, follow-up time and method, and outcome should be recorded in detail. All serious adverse events should be followed up until they disappear, resolve to baseline or ≤ Grade 1, or reach a stable state, or are reasonably explained, or subjects are lost to follow-up, or die.

Below is supplemental information that is included in BMS-Sponsored trials. It is the responsibility of the Sponsor-Investigator to determine if this information regarding hospitalization is considered SAEs or not and whether it should be included in the protocol.

- - a visit to the emergency room or other hospital department < 24 hours, that does not result in admission (unless considered an important medical or life-threatening event)
  - elective surgery, planned prior to signing consent
  - admissions as per protocol for a planned medical/surgical procedure
  - routine health assessment requiring admission for baseline/trending of health status (eg, routine colonoscopy)
  - Medical/surgical admission other than to remedy ill health and planned prior to entry into the study. Appropriate documentation is required in these cases.
  - Admission encountered for another life circumstance that carries no bearing on health status and requires no medical/surgical intervention (eg, lack of housing, economic inadequacy, caregiver respite, family circumstances, administrative reason).
  - Admission for administration of anticancer therapy in the absence of any other SAEs (applies to oncology protocols)

**NOTE**: Although pregnancy and potential drug-induced liver injury (DILI), are not always serious by regulatory definition, these events must be reported within the SAEs timeline.

**NOTE**: Any component of a study endpoint that is considered related to study therapy should be reported as an SAE (eg, death is an endpoint, if death occurred due to anaphylaxis, anaphylaxis must be reported).

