**Expedited and periodic safety update reporting by BMS:**

It is the Sponsor-Investigator’s responsibility to report events to their Local HA. In addition, suspected serious adverse reactions (whether expected or unexpected) shall be reported by BMS to the relevant competent health authorities in all concerned countries according to local regulations (either as expedited and/or in aggregate reports).

In accordance with local regulations, BMS will notify Sponsor-Investigator of all reported SAEs that are suspected (related to the investigational product) and unexpected (ie, not previously described in the IB). An event meeting these criteria is termed a **Suspected, Unexpected Serious Adverse Reaction (SUSAR)**. Sponsor-Investigator notification of these events will be in the form of either a SUSAR Report or a Semi-Annual SUSAR Report. Sponsor-Investigator (or delegate) will receive these reports through the FastTrack portal.

Other important findings which may be reported by BMS as an Expedited Safety Report (ESR) include: increased frequency of a clinically significant expected SAE, an SAE considered associated with study procedures that could modify the conduct of the study, lack of efficacy that poses significant hazard to study subjects, clinically significant safety finding from a nonclinical (eg, animal) study, important safety recommendations from a study data monitoring committee, or Sponsor-Investigator or BMS decision to end or temporarily halt a clinical study for safety reasons.

Upon receiving an ESR from BMS, the Sponsor-Investigator **must review and retain the ESR with the IB**. Where required by local regulations or when there is a central IRB/IEC for the study, the Sponsor-Investigator will submit the ESR to the appropriate IRB/IEC. The investigator and IRB/IEC will determine if the informed consent requires revision. The investigator should also comply with the IRB/IEC procedures for reporting any other safety information.

NON-SERIOUS ADVERSE EVENT COLLECTION AND REPORTING

The collection of non-serious AE information should begin following the subject’s written consent to participate in the study. All non‑serious adverse events (not only those deemed to be treatment-related) should be collected continuously during the treatment period and for a minimum of 100 days following the last dose of study treatment.

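### Adverse-event recording closes about 16 days after surgery, but the two adverse-event-rate endpoints run to day 30 after surgery, and other sections state different windows

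*Protocol*

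**What the plan says.** **When recording ends.** The Follow-up Period section states: "Adverse events should also be recorded until 30 days after the last dose after the end of treatment". The safety visit in the same section is timed "At 30 days (± 7 days) after the last dose of study drug". For serious events, the opening of section 7.2.4 gives the period as "It starts from signing of the informed consent until 30 days (inclusive) after the last dose of study drug". The Overview of investigational product fixes what the clock refers to: "In the study, study drugs are defined as Sintilimab".

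**When surgery happens.** The Dosing Regimen text says "surgery is performed for operable subjects 2 weeks after the last dose".

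**What the endpoints need.** Under Secondary Endpoints, the immune-related rate runs "from commencing of PD-1 inhibition to the 30th day after surgery" and the treatment-related rate "from commencing of treatment to the 30th day after surgery". A third secondary endpoint, surgical complications, also covers 30 days after surgery.

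**Other windows for the same events.**
- Definition of Adverse Events: consent to 30 days after treatment, without saying whether surgery counts as treatment.
- The section on judging the relationship to study drug: consent to the end of the safety follow-up period.
- Later in section 7.2.4, serious events: 100 days after dosing stops.
- Later in section 7.2.4, non-serious events: "for a minimum of 100 days following the last dose of study treatment".

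**The concern.** The endpoint windows are anchored to surgery and the collection windows to the last dose of drug. Surgery comes after the last dose, so a 30-day clock started at the last dose stops before a 30-day clock started at surgery. Someone who follows the Follow-up Period section correctly would stop recording new events while both endpoints are still open.

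Two secondary safety rates are at stake. Unrecorded events can only lower them, and a single-arm trial has no comparator arm with the same omission. Events not collected at the time cannot be reliably recovered later by an analysis rule. Staff also cannot tell from the Protocol which of several stated windows governs.

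**Working it through.** The Protocol states no post-operative closing day, so there is no figure to reproduce. The check is day counting.

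**Inputs**
- Recording closes 30 days after the last dose (Follow-up Period; section 7.2.4, first part).
- Safety visit 30 ± 7 days after the last dose (Follow-up Period).
- Surgery 14 days after the last dose (Dosing Regimen).
- Both endpoints end 30 days after surgery (Secondary Endpoints).
- The last dose is taken as the last sintilimab dose. Chemotherapy ends before sintilimab starts, so counting from a chemotherapy dose would close recording even sooner.

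**Position relative to surgery**
- Recording closes: 30 − 14 = post-operative day 16.
- Shortfall against the endpoint: 30 − 16 = 14 days.
- Safety visit, earliest: 30 − 7 − 14 = day 9. Latest: 30 + 7 − 14 = day 23. Even the latest visit comes before day 30.
- Collection needed after the last dose to reach the endpoint: 14 + 30 = 44 days.
- The 100-day text would reach 100 − 14 = post-operative day 86.

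**Scale of the gap**

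Take sintilimab from day 15 after radiotherapy (Protocol Summary) in three 21-day cycles (Dosing Regimen):
- Last dose: 15 + 2 × 21 = day 57.
- Surgery: 57 + 14 = day 71, or 71/7 = 10.1 weeks. This lies inside the 8 to 12 weeks stated in the Protocol Summary and Overall Design.
- Recording closes: 57 + 30 = day 87.
- Endpoints end: 71 + 30 = day 101. The gap is again 101 − 87 = 14 days.

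Those 14 days are:
- 14/30 = 47% of the post-operative part of each window;
- 14/(101 − 15) = 14/86 = 16% of the whole immune-related window;
- 14/(101 + 35) = 14/136 = 10% of the whole treatment-related window, which adds five weeks of chemoradiotherapy.

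**Effect of one missed subject**

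This assumes rates counted per subject, which Secondary Endpoints does not specify. A subject whose only qualifying event falls in the gap moves a rate by 1/30 = 3.3 percentage points at the sample size in the Protocol Summary, or 1/46 = 2.2 points at the size in the Sample Size section. This is a scale, not an estimate of bias: the Protocol gives no event rate for those days.

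**The case against.** The best defence is the Definition of Adverse Events. It collects to 30 days after treatment, and Overall Design lists radical surgery among the treatments subjects receive. Read that way, collection reaches day 30 after surgery and matches the endpoints. That reading is available, but it does not remove the problem. The Follow-up Period and the opening of section 7.2.4 both count expressly from the last dose, and the only scheduled safety contact follows that clock. Follow-up after that contact is described as imaging and survival.

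Several stronger readings are tempting but not supported:

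- **Late post-operative events go wholly unreported.** The later part of section 7.2.4 asks the investigator to report serious events after the stated periods if believed related to study drug or a protocol procedure. Surgical complications have their own 30-day endpoint, and the Surgical safety section lists 30-day operative mortality, complications and reoperation. Events already open are followed to resolution or stabilisation. The exposure is mainly new-onset, non-serious, immune-related or treatment-related events.
- **Nearly half of the endpoint data are lost.** The 47% applies only to the post-operative days. Against the full windows the share is about 16% and 10%. If rates are per subject, the gap matters only for subjects with no earlier qualifying event.
- **Recording could close on post-operative day 3, or before surgery.** With 21-day cycles and surgery at week 12 (day 84), 87 − 84 = 3. With weekly dosing the last dose is day 29 and recording closes on day 59, while surgery falls on days 56 to 84. These figures set aside the two-week rule, and the weekly ones also draw on a separate contradiction over dosing. They show that those sections need reconciling; they do not measure this gap.
- **Sites would diverge.** The Protocol does not show several sites, and it refers to approval by the ethics committee of one hospital.
- **One hundred days is the Protocol's settled window.** That text concerns reporting to BMS, whereas sintilimab is listed as made by another manufacturer, and nearby text still carries a drafting note about removing what does not apply. It looks like template carry-over, though it is current text.

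**Conclusion.** The inconsistency is real. Under the Follow-up Period rule and surgery two weeks after the last dose, recording closes about post-operative day 16. That is 14 days before the immune-related and treatment-related endpoints end, and the safety visit window cannot bridge the gap. The two rates can be biased low; the direction is clear, but the size cannot be estimated from the Protocol.

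The result assumes that the last dose means the last sintilimab dose and that surgery follows by 14 days. It concerns new-onset events, because those already recorded are followed up. Deleting the 100-day text would remove one competing window and leave the 14-day gap. The primary pCR endpoint is not affected. This is an internal contradiction in the safety windows and does not mean that post-operative safety goes uncollected.

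**What to change.** State one collection window for adverse and serious adverse events, in the same words, in the Follow-up Period, Definition of Adverse Events, the section on relationship to study drug, and every part of section 7.2.4. It should run from consent to at least day 30 after surgery, which is day 44 after the last dose under the two-week rule. Schedule a safety contact at or after that day. The time frames under Secondary Endpoints then fall inside the window and can stay as they are.

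The sponsor should decide on the 100-day text: either keep it and define the end of collection as the later of the two dates, or delete it as carry-over.

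The dosing interval and surgery timing in the Protocol Summary, Overall Design and Dosing Regimen must be reconciled separately. No schedule is proposed here.

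The cost is Protocol and case report form wording, one later safety contact per subject, and somewhat higher reported adverse-event rates.

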# Evaluation

## Efficacy Evaluation

Efficacy endpoints include the following:

- Pathological complete response (pCR) rate based on TRG scoring criteria: refers to the percentage of subjects with TRG grade 0 who have no viable tumor cells remaining in the primary tumor;
- Major pathological response rate (mPR) based on TRG scoring criteria: refers to the percentage of subjects with no vialbe tumor cells (including lymph nodes, stage ypT0N0M0) and single cell or small clusters of tumor cells scattered through fibrosis seen under light microscope;
- Post-neoadjuvant lymph node status (stage ypN) assessed based on AJCC version 8;
- R0 resection rate assessed based on AJCC version 8;
- Disease-free survival (DFS): refers to the time from the start of the postoperative baseline radiographic assessment to the time of disease recurrence or death, whichever occurs first, in subjects who are disease-free following surgery.
- OS: time from the date of enrollment to death due to any cause.

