| **Exclusion criteria** | Patients with any of the following are not to be enrolled in the study:   1. Multiple types of cancer, or accompanied by tumors other than rectal cancer 2. Having received any anti-cancer treatment (surgery, medication, etc.) within the past 5 years 3. Recent history of major surgery 4. Conditions affecting the absorption of capecitabine through the gastrointestinal tract (such as inability to swallow, nausea, vomiting, chronic diarrhea, etc.) 5. Having any type of uncontrolled, severe, accompanying disease, allergic to any component of the study; estimated survival period≤5 years due to any reason 6. Preparing or previously having undergone organ or bone marrow transplantation 7. Receiving immunosuppressive or systemic hormone therapy within 1 month before inclusion for immunosuppression 8. For patients with a history of central nervous system diseases, the investigator needs to judge whether the clinical severity hinders signing the informed consent or affects the patient's oral medication compliance 9. Other situations/problems that may affect the research results or lead to the termination of the study (such as alcohol abuse, drug abuse, etc.) 10. Pregnant or lactating women, or women planning to conceive during treatment |
| **Statistical considerations** | The primary endpoint is pathological complete response (pCR). The trial is designed as a single-arm Phase II study with 80% power to detect an increase in the pCR rate from 5% (historical control for pMMR/MSS LARC after standard long-course radiotherapy) to 20% with a one-sided alpha of 0.05. Accounting for an anticipated 10% drop-out rate, a total of 30 patients will be enrolled. |
| **Period during which study was conducted** | First patient enrolled: 2023-01-01.  Planned enrollment duration: approximately 24 months to accrue ~30 patients.  Planned follow-up after treatment: 5 years (for disease-free survival and overall survival assessments). |

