# Study Endpoints

## Primary Endpoints

Pathologic complete response rate (pCR) based on TRG scoring criteria: refers to the percentage of subjects with no viable tumor cells (including lymph nodes, stage ypT0N0M0) seen under light microscopy.

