### Pathological efficacy evaluation

The surgical specimens are preserved and processed, and the pathological efficacy is assessed according to the TRG scoring criteria; the degree of eradication and ypN staging were assessed according to the AJCC Version 8;

Pathological response evaluation: Based on surgically resected primary lesions, the sites of assessment should include all primary lesions seen by imaging before neoadjuvant therapy, and sections with possible residual tumor cells should be selected for assessment. Viable tumor cells are defined as cells with the ability to proliferate and are graded as follows:

Pathological response evaluation criteria (TRG scoring criteria)*

| Grade 0 (Complete regression) | No viable tumor cells seen under light microscope (including lymph nodes, staging ypT0N0M0) |
| --- | --- |
| Grade 1 (well regression) | Single cell or small clusters of tumor cells scattered through fibrosis |
| Grade 2 (partial regression) | Fibrosis predominates, outgrowing residual tumor |
| Grade 3 (no regression) | Extensive residual tumor, no or little tumor cell necrosis |
| *Remarks: 1) TGR score is limited to the primary tumor bed;  2) Tumor cells refer to viable tumor cells, excluding degenerative and necrotic cells;  3) Large acellular mucinous lakes may appear after radiotherapy/chemotherapy and cannot be considered as residual tumor. | |

Major pathological response is defined as a grade greater than or equal to 1, i.e., grade 0, 1.

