# Statistical analysis of data

## Sample Size

- The primary endpoint is pCR. This study has 80% power to detect an increase in pCR rate from 5% to 20% with a one-sided alpha of 0.05. Considering a 10% drop-out rate, 46 patients will be enrolled.

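### The protocol is inconsistent on whether pCR, the primary endpoint, requires negative lymph nodes, so a ypT0N+ patient can be classified either way

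*Protocol*

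**What the plan says.** Four statements in the Protocol bear on how pCR is counted.

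- **Primary Endpoints:** pCR "refers to the percentage of subjects with no viable tumor cells (including lymph nodes, stage ypT0N0M0) seen under light microscopy".
- **Efficacy Evaluation:** pCR "refers to the percentage of subjects with TRG grade 0 who have no viable tumor cells remaining in the primary tumor".
- **Pathological efficacy evaluation, grade 0 row of the TRG table:** "No viable tumor cells seen under light microscope (including lymph nodes, staging ypT0N0M0".
- **Remark 1 to that table:** "TGR score is limited to the primary tumor bed".

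The paragraph introducing the table also bases the response assessment on the resected primary lesion. No sentence says which statement prevails.

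The design assumptions appear under Sample Size: "This study has 80% power to detect an increase in pCR rate from 5% to 20% with a one-sided alpha of 0.05". The Protocol Summary uses the same rates, power and alpha and enrols 30 patients; Sample Size and Overall Design enrol 46. No test and no responder cut-off are stated.

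On major pathological response (MPR), the section below the table reads: "Major pathological response is defined as a grade greater than or equal to 1, i.e., grade 0, 1".

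**The concern.** The affected patient has a primary tumour bed clear of viable cells but at least one positive node (ypT0N+). Primary Endpoints excludes that patient from pCR. Efficacy Evaluation, read with Remark 1, includes the patient. The two readings are nested: every ypT0N0 patient is a pCR under both, so the tumour-bed reading can add responders and never remove one. Any error therefore runs in the favourable direction.

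The trial is open-label with a single arm, and the result is a small count compared with a fixed historical rate. If the definition is left open, it could be settled once the specimens have been read. The protocol itself states the primary endpoint in two ways, so this is not a detail that can be left to a statistical analysis plan.

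**Working it through.** **1. How each statement classifies a ypT0N+ patient**

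| Statement | Result |
|---|---|
| Primary Endpoints | Not pCR (nodes must be clear) |
| Grade 0 row | Not grade 0; grades 1–3 do not fit either, because each describes residual tumour and the bed has none |
| Remark 1 | Grade 0 (tumour bed only) |
| Efficacy Evaluation, with Remark 1 governing | pCR |
| Efficacy Evaluation, with the grade 0 row governing | Not pCR, and no TRG grade available |

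The conflict therefore lies between Remark 1 and the row it annotates. It reaches the primary endpoint because Efficacy Evaluation defines pCR through TRG grade 0.

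**2. Reproducing the planned size**

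Inputs: null rate 5%, target 20%, one-sided alpha 0.05, power 80%, drop-out 10% (Protocol Summary; Sample Size). Assumed method: exact one-sample binomial test, with p = P(X ≥ r | n, 0.05).

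- The smallest n with alpha ≤ 0.05 and power ≥ 0.80 is 27, with success at r = 4.
- Alpha: 1 − (0.2503 + 0.3558 + 0.2434 + 0.1068) = 0.0437.
- Power: P(X ≥ 4 | 27, 0.20) = 0.8177.
- Drop-out: 27 / 0.9 = 30, which matches the Protocol Summary.

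The match supports the exact test as the likely basis, but the cut-off of 4 is inferred. Because the protocol also states 46, results for that size are shown too.

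**3. One patient at the inferred cut-off**

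| n | At cut-off | One fewer | P(X = cut-off) if true rate is 20% |
|---|---|---|---|
| 27 | 4/27, p = 0.0437 | 3/27, p = 0.1505 | 16.6% |
| 30 | 5/30, p = 0.0156 | 4/30, p = 0.0608 | 17.2% |
| 46 | 6/46, p = 0.0263 | 5/46, p = 0.0786 | 8.0% |

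A single reclassified patient changes the result only if the count sits on the cut-off and a ypT0N+ patient is among those counted.

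**4. Effect on error rates**

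The documents give no ypT0N+ frequency. Assume that a share q of ypT0 patients is node-positive, with q from 5% to 20%.

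*Type I error.* If 5% is the node-inclusive null rate, the tumour-bed null rate is 0.05 / (1 − q).

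| q | Null rate used | n = 27, r = 4 | n = 30, r = 5 | n = 46, r = 6 |
|---|---|---|---|---|
| 0 | 0.0500 | 0.0437 | 0.0156 | 0.0263 |
| 5% | 0.0526 | 0.0512 | 0.0191 | 0.0327 |
| 10% | 0.0556 | 0.0602 | 0.0236 | 0.0409 |
| 20% | 0.0625 | 0.0849 | 0.0367 | 0.0655 |

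At n = 27 the nominal 0.05 is exceeded throughout the assumed range. At n = 30 it is never exceeded, and at n = 46 it is exceeded at 20% but not at 5% or 10%.

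*Power.* If instead 20% is the tumour-bed target rate, the node-inclusive rate is 0.20 × (1 − q). At n = 27 the power of 0.818 becomes 0.782 (q = 5%), 0.742 (10%) or 0.647 (20%). Because the readings are nested, the loss is also the probability that they give opposite verdicts: 0.0355, 0.0757 and 0.1706.

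**The case against.** The strongest reply is that the protocol already leans towards including nodes. Primary Endpoints is the section that defines the endpoint, and it says so. Efficacy Evaluation requires TRG grade 0, and the only definition of grade 0 is the table row that includes nodes. The MPR item just below it also describes complete responders with nodes included. On that reading the sections agree, and Efficacy Evaluation is merely loosely worded.

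Much of this stands. A reader might infer that Efficacy Evaluation makes a ypT0N+ patient a pCR outright. The text does not support that, since it holds only if Remark 1 overrides the grade 0 row. But the reply does not remove Remark 1, which a pathologist could reasonably follow, and it leaves a ypT0N+ specimen without a TRG grade.

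Two further inferences go too far:

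- **That one node-positive patient decides the trial.** The protocol states neither a test nor a cut-off and gives two sample sizes, and a flip needs the coincidence described in step 3. One-patient sensitivity at the boundary is common to small single-arm designs.
- **That the MPR wording matters to the verdict.** On a scale where 0 is best, the inequality alone would select grades 1–3, but the same sentence goes on to list grades 0 and 1, and Efficacy Evaluation describes those two grades in words. MPR is not among the listed primary or secondary endpoints.

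**Conclusion.** The inconsistency on nodal status is real and concerns the primary endpoint, so it should be resolved before the primary analysis. It is conditional: whether a ypT0N+ patient counts depends on whether Remark 1 or the grade 0 row governs, and the protocol does not say. The direction is certain, because the looser reading cannot lower the pCR rate.

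The size is not certain. The p-values illustrate an inferred exact binomial rule. The type I error range of 0.051–0.085 applies to n = 27 and rests on two assumptions: that 5–20% of ypT0 patients are node-positive, and that the 5% historical rate is node-inclusive, which the protocol does not state. At the inferred cut-off for n = 30, the error stays below 0.05 over the same range.

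The MPR inequality is an editorial slip with no bearing on the primary result.

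**What to change.** - Use the Primary Endpoints definition throughout: pCR = ypT0 and ypN0 on the resected specimen.
- Keep TRG as a primary-tumour-bed grade, as Remark 1 says, and remove the nodal wording from the grade 0 row, so that a ypT0N+ specimen has a grade (0).
- In Efficacy Evaluation, state that pCR = TRG grade 0 plus ypN0.
- Editorial: write MPR as TRG grade 0 or 1 (≤ 1).

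The cost is wording only. Surgery records and pathology assessment already requires ypTNM stage, nodal counts and TRG, so no new data are needed and the sample-size inputs do not change. The observed pCR rate may be slightly lower than under the tumour-bed reading. The amendment should be approved before the primary analysis, ideally without reference to the accumulated pathology results.
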